#### Entomological sampling

Mosquito sampling approaches for these observational studies were designed to maximize available vector surveillance resources, and while a priori statistical criteria were not considered, post hoc descriptions of sampling variability and resulting statistical power appropriate to the tests used will be performed.

#### Anthropological sampling

For structured observations, a paired sampling design, whereby villages are chosen to correspond to where entomological surveillance is also happening, is applied. Informants are chosen based on specific activities identified during direct observations. A list of activity groupings is developed to ensure consistency and modified as necessary based on new information from the direct observations. Purposive selection is used to identify informants for interviews, based on their participation in target groups. The number of focus groups is determined from the salient categories; each focus group includes between six and ten participants identified during interactions and conversations with research assistants. Participant observation uses a convenience sampling methodology to observe key activities related to malaria transmission.

#### Sample size in durability monitoring surveys

Sample sizes for the monitoring of ITN physical durability are based on recommendations from [36] and are powered to detect a 9%-to-10%-point difference between locations (products) if the assumed median survival is three years. This represents approximately a 0.5 median survival difference that can be detected as statistically significant [36]. Sample sizes for monitoring ITN insecticidal durability follow WHO recommendation for Phase 3 testing of long-lasting insecticidal nets [38].

### Ethics approval and consent to participate

The current study involves human subjects (epidemiological and anthropological investigations) and nonhuman subjects research (entomological surveillance) in rural communities, as well as secondary use of routine health data. To ensure the safety and well-being of all participants involved in this research, seven institutional review boards reviewed country-specific protocols. In addition, annual reviews will be conducted for the duration of the project to ensure compliance with the methodologies outlined in the protocol.

Prior to entering communities, meetings are organized with the village chiefs, their councils and other relevant authorities, together with the heads of households. Researchers introduce the project and themselves, provide information on who will be conducting which activities, and obtain local authorization.

In all data collection procedures, the participants are informed of the voluntary nature of their participation; of the right to avoid any question with which they may feel uncomfortable; and of their right to withdraw from the study at any time without having to provide a reason and with no consequences for them or their families. Having received an ITN through mass distribution is not a prerequisite for participation.

For the cross-sectional survey, individual informed consent is obtained by trained study personnel from the caregivers of children aged 6 to 59 months at the time of the survey. In Rwanda, consent is obtained from parents/guardians of children aged 6 months to 17 years, assent is obtained from participants aged 7 to 17 years, and consent is obtained from participants aged 18 and older. Individual informed consent is also sought from participants in IDIs, FGDs, and indirect monitoring related to the anthropological component. Consent is sought from the heads of households for structured observations.

The entomological surveillance at homesteads in sentinel villages, though qualified as nonhuman subjects research, requires local leaders and household permission, usually from the head, prior to the performance of any procedure. The granted permission may, for any reason, be withdrawn at any time.

Due to the invasive nature of the observational procedures (access to/inspection of dwellings), especially in anthropological investigations, an initial community sensitization takes place. Any concerns that are brought up during the initial meeting and throughout the study are elevated to the principal investigators to determine if changes need to be made to study procedures. Participant observation is conducted in settings of public activities and does not usually require individual informed consent; however, in the current study, permission is obtained from village chiefs presiding over the public spaces.

### Risks and unexpected adverse events

There is minimal physical and psychological risk associated with this observational study. However, the study team works with the NMCPs and ITN distribution partners to ensure that any potential adverse events related to ITN use are reported appropriately and refers participant concerns to the nearest appropriate health facility.

While severe malaria is not diagnosed as part of study activities, any suspected cases of severe malaria are to be referred immediately to the nearest appropriate health facility. If a household or family member, present at the time of the visit, complains of fever, an RDT will be offered and, if positive, the household member will be offered malaria treatment. If negative, they will be asked to seek medical care as normal. This is not considered part of the research but is done as a broader community benefit. Any unanticipated problem that poses a risk of harm to study participants is reported to all ethics committees within the specified time frame.

The volunteers participating in mosquito collections are screened for malaria infection every two weeks using RDTs and treated with antimalarials if they test positive.

### Analysis and data management

#### Data storage

All data will be de-identified prior to analysis to protect participant confidentiality. Households and participants in cross-sectional and entomological surveys will be assigned unique identification codes. For anthropological research, personal information will be replaced with unique codes assigned to individuals interviewed. The data collected are protected in secure file cabinets or password-protected computers and will be backed up on servers. Electronic data collected on password-protected tablets is transferred, daily, to local servers. Data collection devices are handled only by study staff and kept in a secure location.

#### Epidemiological surveillance analysis

The trials are planned under a superiority, difference-in-differences (DiD) framework. The comparisons will consist of one-sided tests of the null hypothesis that the outcomes (reductions in parasite prevalence or case incidence rate from baseline to end line) in each intervention district are statistically the same as the outcomes in the appropriate control district control arm.

Malaria infection prevalence, determined by RDT tests during the cross-sectional surveys, will be analysed by an appropriate difference-in-differences model comparing changes in prevalence from year to year across study districts (intervention type). Considering sample size constraints, a single indicator age group will be targeted using a clustered sampling approach, clustering observations at a sub-district level (either by sector, health facility catchment, or village—whichever is most practical). Statistical analysis is done using Stata (version 14.2 or later). A difference-in-differences approach will assess matched-pair comparisons of the mean change in malaria prevalence from year to year, before and after ITN distribution across each study districts (intervention/control) comparison. The approach taken within each evaluation setting is powered independently to compare changes in prevalence observed in the ITN intervention districts to changes in the prevalence observed in the appropriate ITN control district. However, given the proposed study design and sampling frame, secondary post-hoc analyses, with Bonferroni’s correction for multiple comparisons, will likely be able to detect an effect size difference of around 20% between any two ITN types at 24 months. The protective efficacy of dual-AI ITNs is determined by multilevel logistic regression model for each year, adjusted for age and individual ITN use the previous night, with clustering at the district level.

For passive case detection (PCD), an observational time-series study design using malaria surveillance data from the district health system will be used to compare trends in malaria case incidence in all age groups using a difference in differences approach. Monthly crude case incidence rates will be calculated at the health facility level by dividing the number of all positive malaria tests (RDT and blood smear) obtained that month by the estimate health facility catchment area population. Appropriate multivariate regression models accounting for the clustering of health facilities by district and for possible confounding factors (e.g., a negative binomial regression analysis of monthly case incidence rates likely to include rainfall amount and health facility catchment area population size), will also be utilized to estimate incidence rate ratios and incremental protective efficacy for IG2, PBO and RG ITNs. Alternatively, test positivity rates (the number of negative and positive test results obtained from suspected cases at the health facility level, stratified by study arm) may also be used to obtain odds ratio estimates from an appropriate logistic regression model. Raw datasets will be cleaned and transformed using Microsoft Excel (Microsoft Corp., Redmond WA) and Tableau v10 (Tableau Software Inc., Seattle WA) and all formal statistical analyses will be done using Stata v14 (StataCorp LLC, College Station TX).

ITN ownership, use, and coverage estimates will be calculated using standard methods recommended by the Surveillance, Monitoring and Evaluation Working Group of the RBM Partnership to end Malaria (https://endmalaria.org/node/990/related-material).

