### Sampling considerations

#### Epidemiological power

The primary epidemiological outcome for which the evaluations are powered is malaria infection prevalence at the district level, as determined by RDTs in children aged 6 months to 5 years and in Rwanda all ages, assessed during annual community cross-sectional surveys. Within each study district, participants were targeted using a clustered sampling approach, clustering observations at a subdistrict level either by sector, health facility catchment, or village—whichever is most practical. Sample size calculations aim at 80% power to detect either a 30% (Burkina Faso and Rwanda) or a 15% (Mozambique and Nigeria) relative reduction in prevalence in an intervention district compared to a 5% reduction in prevalence observed in the standard pyrethroid-only ITN control district [10].

Sample sizes were estimated in PASS 15.0 (NCSS, LLC; Kaysville, Utah) using the following assumptions:Minimum of 15 households sampled per village.An average relative reduction in prevalence of 5% in the standard pyrethroid-only ITN study district.An average relative reduction in prevalence of 30% (Burkina Faso and Rwanda) or 15% (Mozambique and Nigeria) across the 2-year follow-up.Higher than normal estimates of within-cluster standard deviation (0.3) and within-pair variability (CVM = 0.66) to accommodate the likelihood of higher-than-normal homogeneity within non-randomized ‘clusters’.A one-way test with Power = 0.80 and Alpha = 0.0125 (lower than normal to accommodate Bonferroni’s correction for multiple comparisons of the same control district to the different intervention districts).

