One of the strengths of the NNP pilot evaluations is that they take advantage of natural comparisons that arose as the result of normal operational decisions made by partner national malaria programmes. This allows the impact of various ITN deployment strategies (including a formal evaluation of PBO ITNs in West African contexts with high intensity pyrethroid resistance caused by multiple mechanisms) to be evaluated rapidly and in real-world implementation settings, using programmatic data and public health outcomes that are most useful for national stakeholders, both for monitoring progress toward national goals and for informing future vector control decisions. However, the eco-observational, pilot designs also have many important limitations. First, though district-level observations are matched in time and, to the greatest extent possible, in ecology and geography as well, there are challenges in generating supportive datasets needed to account for fundamental differences that may exist between study districts and for potential confounding and/or co-variable factors.

This was particularly true given that campaign ITN procurement and distribution logistics required the stratification and delivery of different ITN types at the district or provincial level, so that all districts—the unit of analysis used here—within a single province typically received the same ITN type. As such, it was necessary to limit these pilot evaluations to contiguous and/or nearby districts from neighboring provinces. This approach to selecting study districts means that baseline comparisons of malaria burden and vector ecology and bionomics varied substantially both within and across the different evaluation settings, capturing real-world diversity in transmission settings but also complicating the interpretation of the observational results. While this does limit their broad generalizability, it is reflective of the diversity in which these products will be taken to scale and will provide insights into the diversity of effectiveness likely encountered through massive scale-up.

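### Survey-based protective efficacy comes from a logistic model for each year with no baseline term listed, so it cannot separate net effect from pre-existing district differences and can contradict the difference-in-differences result

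*Protocol article*

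**What the plan says.** All of the analysis wording is in the protocol article, under Epidemiological surveillance analysis. The overall design is set first: "The trials are planned under a superiority, difference-in-differences (DiD) framework". The hypothesis tests follow it: "The comparisons will consist of one-sided tests of the null hypothesis", applied to reductions from baseline to end line. The survey outcome is treated the same way: infection prevalence "will be analysed by an appropriate difference-in-differences model comparing changes in prevalence from year to year across study districts".

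The last sentence of the same paragraph sets a different rule for efficacy: "The protective efficacy of dual-AI ITNs is determined by multilevel logistic regression model for each year, adjusted for age and individual ITN use". Net use here means use on the night before the survey, and the model is specified "with clustering at the district level". The listed adjusters are age and previous-night net use. Baseline prevalence, survey round and a net-type-by-round term are not among them.

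Three other places bear on this:
- Study design, and Identification of intervention and control study districts: the national programmes decided which net went where, so allocation was not random.
- Table 1: within each evaluation, each new net type is represented by one district.
- Discussion: "baseline comparisons of malaria burden and vector ecology and bionomics varied substantially both within and across the different evaluation settings". It later names measured baseline differences only as one possible local addition to a common analysis framework.

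**The concern.** A model fitted to one survey year compares districts as they stand in that year. If the control district started with more malaria than the intervention district, the gap appears as protection. If it started with less, the gap appears as harm. Difference-in-differences removes a fixed gap of this kind, but the efficacy sentence as written does not use it.

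The district-level clustering does not help. With one district per net type in an evaluation, district and net type coincide within a year, so a district random effect cannot be told apart from the net effect.

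The report could therefore carry two survey results for the same net that disagree in size or even in sign, with the second labelled protective efficacy. The direction of the error would also vary by country, so the efficacy figures would not be comparable across the evaluations.

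**Working it through.** The article states no efficacy figure, so there is none to reproduce. The check asks what a single-year comparison returns when the new nets add nothing, and what it returns at the planned effect.

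**Inputs**
- RDT baselines for intervention (b_i) and control (b_c): Table 1.
- Control change, from Epidemiological power: "An average relative reduction in prevalence of 5% in the standard pyrethroid-only ITN study district".
- Planned intervention change, same section: 30% relative reduction in Burkina Faso and Rwanda, 15% in Mozambique and Nigeria.
- Assumption: efficacy is read as 1 minus the odds ratio, the direct output of a logistic model. The article does not state the scale.
- Assumption: each evaluation is modelled on its own.
- Not modelled: adjustment for age and net use, for which the article gives no data.

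**Formulas**
- odds(p) = p/(1 - p)
- Baseline OR = odds(b_i)/odds(b_c)
- Single-year efficacy = 1 - odds(f_i)/odds(f_c), where f is follow-up prevalence
- Efficacy with baseline included = 1 - (follow-up OR)/(baseline OR), the district-by-period term of a logistic difference-in-differences model

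**Step 1: no net effect, prevalence unchanged**

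| Pair | b_i v b_c (%) | OR | 1 - OR |
|---|---|---|---|
| Banfora IG2 v Gaoua | 13.8 v 32.4 | 0.334 | 67% |
| Orodara PBO v Gaoua | 13.6 v 32.4 | 0.328 | 67% |
| Karongi IG2 v Nyamagabe | 3.1 v 14.4 | 0.190 | 81% |
| Asa IG2, Moro RG v Ejigbo | 43.7 v 54.9 | 0.638 | 36% |
| Cuamba IG2, Mandimba RG v Gurue | 48.6 v 44.3 | 1.189 | -19% |
| Guro IG2 v Chemba | 47.6 v 29.4 | 2.181 | -118% |
| Changara PBO v Chemba | 29.4 v 29.4 | 1.000 | 0% |
| Ife North PBO v Ejigbo | 54.9 v 54.9 | 1.000 | 0% |

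Example, Banfora: (0.138/0.862)/(0.324/0.676) = 0.1601/0.4793 = 0.334.

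**Step 2: both districts fall by 5%, then the planned effect**

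| Pair | Both fall 5%: single year | Both fall 5%: with baseline | Planned effect: single year | Planned effect: with baseline |
|---|---|---|---|---|
| Banfora IG2 | 66% | -1.6% | 76% | 28% |
| Orodara PBO | 67% | -1.6% | 76% | 28% |
| Karongi IG2 | 81% | -0.7% | 86% | 26% |
| Asa IG2, Moro RG | 35% | -2.1% | 46% | 15% |
| Cuamba IG2, Mandimba RG | -18% | 0.7% | 3% | 19% |
| Guro IG2 | -113% | 2.4% | -75% | 20% |
| Changara PBO | 0% | 0% | 14% | 14% |
| Ife North PBO | 0% | 0% | 20% | 20% |

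Example, Guro at the planned effect:
- f_i = 0.476 x 0.85 = 0.4046, odds 0.6795
- f_c = 0.294 x 0.95 = 0.2793, odds 0.3875
- Follow-up OR = 0.6795/0.3875 = 1.75, so single-year efficacy is -75%
- Ratio to baseline OR = 1.75/2.181 = 0.80, so efficacy with baseline is 20%

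The small non-zero values with baseline included arise because equal relative falls in prevalence are not equal falls in odds.

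**The case against.** The strongest reply is that the main inference does not depend on this sentence. Infection prevalence is the powered outcome ("A one-way test with Power = 0.80 and Alpha = 0.0125"), and both the prevalence comparison and the one-sided tests are difference-in-differences. The efficacy sentence carries no test, alpha or power. Cost-effectiveness draws on incidence rate ratios from routine data, not on survey efficacy. All of this stands. A reader might infer that the yearly figure is the study's headline result, or the one programmes and donors will quote; nothing in the article says so.

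Second, one sentence in an article may compress a fuller model, the Discussion allows for local handling of baseline differences, and yearly models might include the baseline round. That is possible. But the sentence names its adjusters and baseline is not one, and the Discussion lists it only as a possibility. Showing a baseline-year odds ratio beside the later ones would reveal the gap without removing it.

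Third, the sizes are soft. The note under Table 1 says the surveys were not done at study-area level, several districts share one value, and the values are for under-5s whereas Rwanda surveys all ages. This stands: the figures illustrate and do not forecast, and two of the PBO pairs show no gap at all.

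Fourth, a reader might infer that the plan equates 1 minus the odds ratio with a relative reduction in prevalence, or that adjusting for net use is an error. The article never defines efficacy as 1 minus the odds ratio. Net use may differ between non-randomised districts for reasons unrelated to net type, so adjusting for it can be defended. It is also measured after distribution, so adjustment would remove part of the effect if net type influences use. That is a choice to make visible, not a demonstrated fault.

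**Conclusion.** The point holds for survey-based protective efficacy only. As written, the efficacy model cannot distinguish what the nets did from how the districts already differed, and it sits in the same paragraph as an analysis built to make that distinction. On Table 1 values, nets that add nothing would show anything from -118% to 81%. The error would favour the new nets in Burkina Faso, Nigeria (IG2 and RG) and Rwanda, count against them in northern Mozambique and Guro, and be nil in Changara and Ife North. Including baseline brings every no-effect result to within about 2.5 percentage points of zero.

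These sizes rest on Table 1 standing in for the true district baselines, on the odds-ratio scale, and on leaving out the age and net-use adjustment. The conclusion that the two analyses can disagree needs only non-random allocation, one district per net type, and the baseline differences that the Discussion concedes.

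**What to change.** Replace the efficacy sentence so that, for each evaluation:
- protective efficacy comes from one model fitted to all survey rounds including baseline, using the net-type-by-round term, adjusted for age;
- clustering is at the sub-district sampling unit (sector, facility catchment or village), as the survey design already has it;
- the scale on which efficacy is reported is stated;
- results are shown with and without adjustment for previous-night net use;
- single-year comparisons between districts, if kept, are labelled descriptive.

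No new data are needed, since Table 3 gives each country a first survey round around its distribution. The cost is wider intervals, because baseline sampling error enters the estimate. One limit should be reported with the result: Tables 2 and 3 put the first Burkina Faso survey in July 2019, after the PBO distribution was completed in June 2019, so the Orodara baseline is not a clean pre-distribution value.

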*Prevalence surveys were not conducted at the study area level. Details on each survey methodology can be found in the referenced document for each country. Additional details on each evaluation context are available in Additional file 2: Annex S1

^†^Indicates study control area

IG2s were deployed in five districts (Burkina Faso, Nigeria, western and northern Mozambique, Rwanda), RGs deployed in two districts (Northern Mozambique and Nigeria) and PBOs deployed in three districts (Burkina Faso, Western Mozambique, and Nigeria). In Rwanda, one district deployed IRS in combination with standard pyrethroid-only ITNs in comparison to pyrethroid-only ITNs alone (Figs. 1, 2, 3 and 4).

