### Identification of intervention and control study districts

Decisions on what brand/type of ITN to procure, and where to distribute them were made by each respective NMCP through consultation with partner institutions and international donors. The NMCPs used the dual-AI ITNs in their mass campaigns with the stipulation that there be an accompanying pilot evaluation based on their distribution and the study designs took advantage of natural comparisons among districts that results from these decisions. The NMCPs of Burkina Faso (2019) and Rwanda (2020) incorporated IG2 ITNs into their mass distribution campaigns. Mozambique and Nigeria both incorporated IG2 and RG ITNs into their 2020 mass campaigns. In addition, Burkina Faso (2019), Mozambique (2020), and Nigeria (2020) incorporated PBO ITNs into their mass campaigns. All districts included in the mass distribution campaigns receive a single type of net. A subset of districts that receive IG2, RG, PBO, and pyrethroid-only ITNs were selected by the partners as study districts (Table 2).

**Table 2 Tab2:** ITN distribution by country National Malaria Control Programmes

Geography	Study period	ITNs evaluated	ITN distribution completed
Burkina Faso	2019–2022	IG2, PBO	June 2019 (PBO) August 2019 (standard) October 2019 (IG2)
Northern Mozambique	2020–2022	IG2, RG	November 2020
Western Mozambique	2020–2022	IG2, PBO	December 2020
Rwanda	2020–2022	IG2	February 2020 (standard) May 2020 (IG2)
Nigeria	2020–2022	IG2, RG, PBO	November 2020

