### Epidemiological component

Across all countries, malaria burden is measured through cross-sectional surveys, routine health facility data, and in most evaluations, antenatal care surveillance. For all countries, the study aims to conduct all surveys during high transmission seasons. This is complicated in many areas because of seasonal rains that impact operations. In addition, because of the timing of the grant and the net distribution, with the necessity to conduct a baseline survey before or contiguous with distribution, the timing of baseline surveys were adjusted in Rwanda, Nigeria, and Mozambique. Efforts are made to ensure that the post distribution cross-sectional survey timing is within a higher transmission season and is consistent across the years for comparison. In Burkina Faso, where four rounds of SMC are done annually in children 3 months to 5 years during the malaria transmission season, the study aims to time the surveys before SMC campaigns to ensure that the measurements are not conflated with the effects of the first round of seasonal malaria chemoprevention.

In each study district, villages were randomly selected for participation using probability proportionate to size, from which households were sampled either randomly or following a standard systematic sampling approach (e.g., every third household) During each survey a new set of households with eligible participants are selected (Table 3).

**Table 3 Tab3:** Cross-sectional survey methodology by country

Country	Participants		Sample size (households)	Survey months
	Questionnaire	Prevalence		
Burkina Faso	Household head or primary caregiver	Child aged 6 to 59 months	570 per year (2280 total)	• July 2019 • July 2020 • July 2021 • July 2022
Northern and western Mozambique	Household head or primary caregiver	Child aged 6 to 59 months	2520 per year (7,560 total)	• September–October 2020 • September–October 2021 • August–September 2022
Nigeria	Household head or primary caregiver	Child aged 6 to 59 months	1680 per year (5,040 total)	• September 2020 • November 2020 • November 2021
Rwanda	Household head or primary caregiver	All household residents aged 6 months and older	450 per year (1,800 total)	• February 2020 • December 2020 • November 2021 • November 2022

*LGA* local government area

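### The yearly protective-efficacy model clusters on district, which coincides with net type in each evaluation, and leaves out the villages that were actually sampled

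*Protocol article*

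**What the plan says.** All statements are in the Protocol article.

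- Epidemiological surveillance analysis, on the model: "The protective efficacy of dual-AI ITNs is determined by multilevel logistic regression model for each year", and it is "adjusted for age and individual ITN use the previous night, with clustering at the district level". No village or household level is named.
- The same section, earlier in the paragraph, describes the survey sample as "clustering observations at a sub-district level (either by sector, health facility catchment, or village—whichever is most practical"). Epidemiological power describes the sample the same way.
- Epidemiological component, on sampling: "In each study district, villages were randomly selected for participation using probability proportionate to size". Households are then drawn within villages. In Rwanda all residents aged 6 months and older are tested.
- Identification of intervention and control study districts: "All districts included in the mass distribution campaigns receive a single type of net".
- Study sites, for example: "IG2s were deployed in five districts (Burkina Faso, Nigeria, western and northern Mozambique, Rwanda"), that is, five IG2 districts over five evaluations. Table 1 shows three districts in each evaluation and four in Nigeria, with each intervention listed once.
- Epidemiological power: at least 15 households per village, a within-cluster standard deviation of 0.3, a within-pair coefficient of variation of 0.66, and a one-sided alpha of 0.0125 with 80% power.

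**The concern.** A clustering level is useful only if there are several clusters per arm. Here there is one district per arm in each evaluation, so the level named in the model cannot supply a variance, and the level that could supply one is absent. Software would still return an estimate and an interval, and nothing in the output need show that the interval ignores all clustering. Protective efficacy is one of the figures meant to inform national programmes and donors. Intervals that are too narrow would make some net comparisons look more certain than the data allow.

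**Working it through.** **Step 1. Districts per intervention (Table 1).** Burkina Faso, northern Mozambique and western Mozambique each have three districts and three net types. Nigeria has four and four. Rwanda has three districts, two of them with the same pyrethroid-only net, but one of these also has IRS, so each distinct intervention still has one district.

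**Step 2. Can a district random intercept be estimated?** With net type as a fixed effect, the fixed part already fits one level per district, so nothing is left for a district variance to explain. A check on illustrative counts (3 districts of 190 children) gives this profile log-likelihood by district standard deviation (logit scale):

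| District SD | 0 | 0.1 | 0.3 | 1.0 |
|---|---|---|---|---|
| Profile log-likelihood | -7.74 | -8.12 | -9.62 | -12.67 |

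The maximum is at zero, so the fit becomes ordinary logistic regression on independent children.

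**Step 3. Would district-robust errors rescue it?** No. In simulations with age and net use as covariates and three districts, the district-robust standard error of a net-type contrast was typically about 2 to 4% of the ordinary one. It is unusable, because residuals nearly cancel within each district once net type is fitted.

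**Step 4. What the sample size assumes.** Take the matched-pair cluster formula with villages as clusters:

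K = 2 + (z0.9875 + z0.80)² × [2 × 0.3²/m + 0.66² × (μ1² + μ2²)] / (μ1 − μ2)²,

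where (2.241 + 0.842)² = 9.505, m is households per village, and μ1 and μ2 are the stated relative reductions. The per-district figures are Table 3 divided by the number of districts.

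| Setting | Reductions | m | K | Villages × m | Table 3 per district |
|---|---|---|---|---|---|
| Rwanda | 0.05, 0.30 | 15 | 9.95 | 10 × 15 = 150 | 450/3 = 150 |
| Burkina Faso | 0.05, 0.30 | 19 | 9.57 | 10 × 19 = 190 | 570/3 = 190 |
| Mozambique, Nigeria | 0.05, 0.15 | 20 | 20.91 | 21 × 20 = 420 | 2520/6 = 1680/4 = 420 |

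The 15 in Rwanda is the stated minimum. The 19 and 20 are assumptions chosen to match; at m = 15 the formula gives 150 in Burkina Faso and 24 × 15 = 360 in Mozambique and Nigeria. The sample size is thus consistent with villages as the clusters, and the efficacy model does not carry that level.

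**Step 5. Size of the error when village clustering is left out.** Inputs: m = 15 children per village (the stated minimum) and an assumed intracluster correlation (ICC). Design effect = 1 + 14 × ICC; standard-error factor = √(design effect); true one-sided error = 1 − Φ(2.241/factor).

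| ICC (assumed) | Design effect | SE factor | True error at nominal 0.0125 |
|---|---|---|---|
| 0.02 | 1.28 | 1.13 | 0.024 |
| 0.05 | 1.70 | 1.30 | 0.043 |
| 0.10 | 2.40 | 1.55 | 0.074 |

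At m = 20 the true errors are 0.028, 0.054 and 0.094. A null simulation of the model without village clustering, with a latent-scale ICC of 0.05 to 0.20 and no true district variation, gave 0.019 to 0.100, in line with this.

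In Rwanda the number tested per village exceeds the number of households because all residents are tested, so the error is larger at the same ICC. The article gives no household size, so I put no figure on it.

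**Step 6. Few villages.** With 10 villages of 19 and an ICC of 0.05, simulated error was 0.060 without village clustering and 0.023 with uncorrected village-robust errors. Village clustering removes most of the excess, but about ten villages per district also calls for a small-sample correction.

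**The case against.** The strongest reply is that the quoted sentence covers one model only. Prevalence, the powered outcome, is to be analysed by a difference-in-differences model described only as appropriate, with sub-district clustering mentioned beside it. The Discussion also refers to a common analysis framework that is not shown. This stands, and it limits the point to the yearly efficacy model. It does not rescue that model, whose clustering level the article states outright. Pooling all 16 districts would make a district variance estimable in principle, but comparisons are planned within each evaluation.

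A reader might infer more than the article supports:

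- **That the incidence model has the same fault.** The phrase there is "accounting for the clustering of health facilities by district". It can mean simply that facilities are nested in districts. Rates are computed per facility, and the regression is given only as an example.
- **That the matched-pair comparison has one pair and no degrees of freedom.** The Discussion does say "all districts—the unit of analysis used here—within a single province typically received the same ITN type", but while explaining procurement logistics. Villages as clusters reproduce the sample size, which argues against a one-pair reading.
- **That the two clustering phrases flatly contradict each other.** One belongs to the sampling description and the other to a model. They are a mismatch to reconcile.
- **That error rates are inflated further by chance differences between districts.** Such differences may exist, but they are confounding of district with net type. Village clustering would not remove them, and the Discussion already discloses them as a limitation.

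**Conclusion.** The yearly protective-efficacy model is wrong as written. Its only named clustering level coincides with net type within every evaluation, and it omits the village level on which sampling and sample size rest. Followed literally, it gives standard errors that are too small by a factor of about 1.13 to 1.55 for an ICC of 0.02 to 0.10 at 15 children per village, and a one-sided error of 0.024 to 0.074 in place of 0.0125. At the low end the understatement is modest, so a blanket statement that the standard errors are far too small is not supported.

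The structural part rests on Table 1 alone and needs no assumption beyond fitting within each evaluation. The size rests on assumed ICCs. No claim is made about the difference-in-differences or incidence models.

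**What to change.** In the efficacy-model sentence:

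1. Replace district clustering with a village random intercept or village-clustered errors, with a small-sample correction where villages are few.
2. Add a household level in Rwanda.
3. Enter district/net type as a fixed effect only.
4. Reconcile the sentence with the sub-district clustering described in Epidemiological power and earlier in the same section, naming the unit used in each country.
5. State that within-evaluation intervals and p-values exclude between-district variation, which cannot be separated from net type with one district per intervention.

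A pooled analysis of the five IG2 comparisons is optional. The evaluations differ in vector, resistance and surveyed ages, so pooling would mix real differences in effect with district variation.

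The cost is wording and model code. No new data are needed, provided village and household identifiers are kept in the survey data. The downside is wider intervals.
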